### Adverse Events Reporting and Compliance Enhancement

From week 0 to week 10, detailed records of adverse events (AEs) will be documented, including type, occurrence time, severity, and duration. In the event of visual impairment, skin injuries, fainting, infections, or other serious AEs, treatment will be discontinued, and the participant will be transported to the nearest hospital. A detailed AE report will be submitted to the Ethics Committee. At the conclusion of the follow-up period, children are entitled to receive 3 sessions of pediatric *tuina* therapy at no cost; however, those who withdraw prematurely are not eligible for this benefit.

### Data Management and Quality Control

In this study, the basic information of each participant includes gender, age, height, weight, medical history, current condition, and contact information for parents or legal guardians. Researchers promptly complete the case report form (CRF) for each participant, including UCVA, SE, AL, AMP, concomitant medications, dropout status, and AEs (such as blurred vision, photophobia, etc). Regardless of whether these AEs are related to the treatment of this study, participants will receive appropriate management and timely documentation, which we record in detail in the CRF. Four rounds of outcome data are collected from baseline to the end of follow-up. Completed CRF forms from 4 hospitals are sent to the Department of Tuina Basic Education of the Second Clinical Medical College of Yunnan University of Chinese Medicine. Two members who are unaware of the grouping status will conduct double data entry and aggregate the data into an electronic dataset. Simultaneously, the data administrator monitors and checks for any procedural errors. Unblinding is permissible after the completion of the experiment. The Data Monitoring Committee is independent of the sponsor and has no conflicts of interest.

### Ethical Considerations

The trial has been registered on the Chinese Clinical Trial Registry (ChiCTR2600116606). At the onset of this study, we submitted an application to the Chinese Clinical Trial Registry Center; however, the review process took an extended period of time, resulting in registration occurring only after the recruitment and data collection had commenced. This study was approved by the Ethics Committee of the Second Affiliated Hospital of Yunnan University of Chinese Medicine (2024‐050) and conforms to the Declaration of Helsinki. It will be ensured that participants actively provide informed consent or discuss and make decisions with trusted family members. All participants’ personal identification information, including names, telephone numbers, identification numbers, and medical records, is anonymized to prevent information leakage. Researchers store all participants’ data in a dedicated cabinet and retain them for at least 5 years after publication. The Ethics Committee of Yunnan University of Chinese Medicine will regularly review the progress of the trial and supervise the collection, distribution, and confidentiality of the data. The committee can implement modifications or termination of the trial. The use of all personal photographs has been approved by the individuals concerned and their guardians, and informed consent forms have been signed (Multimedia Appendix 2). Upon completion of the treatment and follow-up, the participants will be provided with 3 iterations of *tuina* therapy at no cost. Participants who withdraw before completion will not be eligible for this benefit. All treatments and tests received by participants are free of charge. Participants will be allowed to withdraw at any time, and their subsequent treatment will not be affected in any way.

## Results

As of December 2025, 29 participants have been enrolled, with 16 allocated to the *tuina* experimental group and 13 allocated to the drug-positive control group. The current data indicate that *tuina* therapy is helpful in enhancing UCVA and improving AL of eyes, with no AEs reported, suggesting that *tuina* therapy is an effective alternative treatment. The enrollment process will continue until October 2026. We will submit the final manuscript before December 2026, following which we will disseminate the final results in accordance with the CONSORT checklist.

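### A favourable conclusion on both primary outcomes and adverse events is published with 33 of 62 children still to enrol; it appears inconsistent with the blinding rules and the data cannot support it

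*Protocol article*

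**What the plan says.** The Results section of the protocol article gives the recruitment status: "As of December 2025, 29 participants have been enrolled, with 16 allocated to the" tuina group and "13 allocated to the drug-positive control group". It goes on to say, from the data so far, that tuina "therapy is helpful in enhancing UCVA and improving AL of eyes, with no AEs reported", and infers that tuina "therapy is an effective alternative treatment". It then adds: "The enrollment process will continue until October 2026". The Results paragraph of the Abstract gives the enrolment counts without any statement on outcome.

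Four other places bear on this:

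- Data Management and Quality Control: "Unblinding is permissible after the completion of the experiment". Also: "Two members who are unaware of the grouping status will conduct double data entry". An independent Data Monitoring Committee is mentioned, but not as the source of the statement in Results.
- Abstract, Methods: statisticians are to be blinded. UCVA and AL are named as the primary outcomes.
- Randomization and Blinding: outcome assessors are blinded, including for the analysis of results. Therapists and parents are not. The hospital heads recruit, and they also assign children to groups.
- Study Design: a noninferiority trial with 8 weeks of treatment and 2 weeks of follow-up per child. No interim analysis is described here or elsewhere in the article.

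**The concern.** A statement that one treatment helps on both primary outcomes needs outcomes linked to allocation. The article's rules place that link after completion and keep the analysis blinded. Either someone has looked at outcomes by group, or the sentence rests on impressions from staff who know the allocation. Neither is a planned source of evidence in this trial.

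The practical risk lies in the 33 children still to be enrolled and in those still under assessment. The people who recruit, allocate and treat them, and their parents, can now read that one arm works and has produced no adverse events. UCVA depends on the child's effort. Families may withdraw at any time. Whoever recruits and also allocates can be influenced in whom to approach. Expectation can therefore enter through measurement, through unequal dropout and through selection.

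There is also a question of credibility. The trial is described as noninferiority, and the article shows no margin and no order between its two primary outcomes. Once a favourable look is in print, the sponsor will need to show that those choices came before it.

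**Working it through.** **1. The passages side by side.** The Results section attributes a benefit to tuina on UCVA and AL. Data Management and Quality Control, read naturally, does not allow unblinding before completion. The Abstract blinds the statisticians, and Randomization and Blinding extends assessor blinding to result analyses. No section describes an interim look that would reconcile these.

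**2. How far the trial had got.** Enrolled: 29/62 = 46.8%. Still to enrol: 62 − 29 = 33, or 53.2%. These are enrolment fractions. Each child needs 8 + 2 = 10 weeks, or 70 days. If the cut-off was 31 December 2025 (an assumption; only the month is given), a child enrolled after about 22 October 2025 could not have finished. The number with outcome data is not stated and must be taken as at most 29.

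**3. The plan's own sample size.** The Sample Size section uses an effect size of 0.8, read here as a standardised difference d, with two-sided α = 0.05, 80% power and 1:1 allocation. For a two-sample t test, power comes from the noncentral t with df = 2n − 2 and noncentrality d × √(n/2):

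- n = 25 per arm: 79.1%
- n = 26 per arm: 80.7%

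So 26 per arm, 52 in all, is reproduced, and d = 0.8 is the right input for the next step.

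**4. What 16 v 13 can show, if every enrolled child had an outcome.**

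- √(1/16 + 1/13) = 0.373
- Noncentrality = 0.8/0.373 = 2.14 with df = 27, giving power of about 54%
- 95% CI half-width = 2.052 × 0.373 = 0.77 SD, against 0.51 SD at 31 v 31

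These are best cases, because fewer children can have completed.

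**5. What no adverse events can show.** With 0 events in n children, the upper limit is 1 − a^(1/n), where a = 0.025 for a two-sided 95% interval and a = 0.05 for a one-sided 95% bound.

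| Children | Two-sided 95% limit | One-sided 95% bound |
|---|---|---|
| 16 (tuina arm) | 20.6% | 17.1% |
| 29 (both arms) | 11.9% | 9.8% |

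The second row is shown because the sentence does not say which arm its count refers to.

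**6. Type I error, conditional.** Suppose the look had been a two-sided test at 0.05 that could have led to a success claim or early stop, followed by an unadjusted final test at 0.05. With correlation √(29/62) = 0.684 between the two statistics, the overall two-sided error is about 0.084. It runs from 0.081 at an information fraction of 29/52 = 0.56 to 0.091 at 0.25. The document states no such test or option.

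**The case against.** The best defence is that the article does not say the code was broken. It gives no estimate, no test and no contrast between arms. Therapists and parents know the allocation by design and the hospital head assigns it, so site staff could form this view without any formal unblinding. That stands. A reader might infer that the unblinding rule has been broken; the document supports an apparent inconsistency, not an established breach.

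Several other limits also stand:

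- **Type I error.** A reader might conclude that it is now 8.4%. A look with no option to claim success or stop spends no alpha, and none is stated. The figure also describes tests of difference, while the trial is called noninferiority.
- **Bias.** A reader might say the remaining half is biased. The text supports a risk only. AL is an instrument reading and assessors are stated to be blinded, so the risk is clearest for UCVA, retention and enrolment.
- **Margin and endpoint.** A reader might call these unset. A condensed article shows only that they are not stated there; a fuller document dated before the look could settle the matter.
- **Safety.** The absence of adverse events is reported as a count, and the inference drawn is about effectiveness. The limits in step 5 show how little the count excludes.
- **Late registration.** The article discloses openly that the review took a long time, "resulting in registration occurring only after the recruitment and data collection had commenced". It is a separate matter. It bears here only because the registry entry cannot show that choices were fixed before data collection began.

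None of this rescues the sentence. No other section explains or licenses it, and it draws a treatment conclusion while recruitment is open.

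**Conclusion.** The point holds in this form. A treatment conclusion on both primary outcomes, with a favourable remark on adverse events, was published at 46.8% of planned enrolment. No interim look is described, and the statement appears inconsistent with the stated blinding of analysis and the timing of unblinding.

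The evidence behind it is at best 16 v 13 children: about 54% power for the planned difference, a CI half-width of 0.77 SD, and an adverse event rate in the tuina arm that could be as high as 20.6%. The efficacy figures assume that d = 0.8 is a standardised mean difference and that all 29 children had outcomes; the second assumption flatters the data.

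The risk of expectation bias is credible because recruiters, allocators, therapists and families are unblinded, but the document gives nothing from which to compute its size. The 8.4% remains hypothetical unless the sponsor discloses that the look could have led to a success claim or early stop.

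**What to change.** 1. Delete the efficacy and adverse event sentence from Results and report enrolment only.
2. Disclose the matter as an unplanned look: who saw which arm-level data, when, for how many children with outcomes, and whether any decision followed. The sponsor should report what happened; the document does not establish that no decision was taken.
3. State that arm-level outcome data go only to the existing Data Monitoring Committee until database lock.
4. Document, with dates, that the primary endpoint and the noninferiority margin predate the look. If that cannot be shown, fix them now from external evidence and say so.

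A comparison of children enrolled before and after the disclosure should be left out or labelled descriptive. If the split falls at 29, the later children would be 15 v 18, and the standard error of the difference between the two effects is √(1/16 + 1/13 + 1/15 + 1/18) = 0.51 SD. Detecting a shift with 80% power would need about 2.80 × 0.51 = 1.4 SD, so a null result would reassure no one.

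The cost is wording, a short disclosure and some record keeping. No visits, measurements or children are added. The change is worth most while enrolment is still open.

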## Discussion

### Expected Findings

This study aims to evaluate the efficacy and safety of *tuina* therapy through a randomized controlled clinical trial. We anticipate that children who receive *tuina* therapy will show improvements in AL, UCVA, SE, and AMP that are not inferior to those achieved through drug therapy. Furthermore, we expect that *tuina* therapy will be safer, free of adverse effects, and exhibit more stable long-term efficacy.

The high prevalence and severe complications of myopia have inflicted significant damage on the visual health of adolescents, imposing a substantial burden on both society and the economy. Therefore, the urgent need for an effective method to prevent and control myopia is evident. *Tuina* is a potential alternative therapy for myopia. However, current research on the application of *tuina* therapy for myopia predominantly focuses on local ocular areas, neglecting the holistic perspective, which to some extent limits its therapeutic efficacy. The holistic perspective is a fundamental concept in TCM, which views the human body as an integrated whole. This perspective posits that the human body is a harmonious entity, with the heart as the master and the 5 organs at the center, interconnected through the meridian system. This holistic entity is indivisible in terms of structural integration, functionally coordinated, and pathologically interrelated. Consequently, in the rehabilitation of myopia, it is imperative not only to address local symptoms around the eyes but also to promote the overall regulation of the child’s body.

During our long-term clinical practice, we have observed that children with myopia exhibit corresponding abnormalities at specific acupoints on their backs, such as BL 13, BL 15, BL 18, BL 20, BL 23, and their surroundings. These abnormalities include the presence of cord-like or nodular reactive substances, or localized temperature decreases. Selectively stimulating these abnormal reaction points on the back acupoints (or regions) can effectively improve the visual acuity of children. Further research has revealed that the acupoints of the first lateral line of the BL are highly congruent with the dermatomal projections of the spinal nerve roots on the surface of the body. Based on these findings, we have integrated the holistic perspective of TCM with the anatomical principles of spinal nerves in Western medicine, thereby establishing “selective spinal *tuina* manipulation therapy.” This technology system consists of 4 steps: the first and fourth steps focus on overall regulation, while the second and third steps emphasize localized treatment. This approach achieves a combined model of diagnosis and treatment that integrates both global and local care, leading to the restoration of vision.

The first step is comprehensive treatment to achieve overall rehabilitation objectives. The principle underlying this approach is the stimulation of the GV and the Bladder Meridian, which is closely associated with the regulation of visceral functions. According to *《Yin Hai Zhi Nan》*, “In treating the eyes, one cannot afford to overlook the Bladder Meridian.” The Bladder Meridian is the meridian with the highest number of acupoints in the human body. Each internal organ corresponds to a specific acupoint on this meridian. By stimulating the acupoints on this meridian, one can regulate the body’s neural and humoral functions, enhance the body’s *qi*, and achieve the purpose of preventing disease [31]. The second step involves selective stimulation of back sensitized acupoints or regions to achieve personalized and precise rehabilitation objectives. The sensitization of acupoints refers to the transition from a “quiescent” (physiological state) to an “activated” (pathological state) condition, primarily manifesting as abnormalities in morphological, thermal, and electrophysiological indicators. By stimulating abnormal back acupoints, the regulation of visceral functions can be achieved. The third step involves addressing common symptoms associated with myopia, such as blurred vision and visual fatigue, through local massage stimulation around the eye area. This can help to relax muscles, promote blood circulation, and enhance vision. A meta-analysis on the selection rules of acupoints for myopia indicates that local eye acupoints such as BL 1, BL 2, and ST 2, which have branches of the supraorbital nerve, oculomotor nerve, and facial nerve, as well as the orbital vessels and nerves, may promote increased blood flow to the eyes, enhance orbital blood supply, and stimulate orbital nerves to regulate, thereby coordinating the contraction and relaxation of eye muscles and exerting regulatory effects on myopia [32,33]. Fourth, harmonizing *yin* and *yang* involves stimulating acupoints along the GV and related specific points on the head and face, further promoting overall rehabilitation. Stimulating acupoints on the head and face can enhance cognitive function and calm the mind, while rubbing the back along the GV and Bladder Meridian can regulate the flow of *qi* throughout the body, adjusting the functions of the organs. By integrating these methods, the circulation of blood and *qi* can be promoted, and *yin* and *yang* can be harmonized, ultimately achieving the rehabilitation of myopia.

### Innovations and Limitations

It should be noted that this study also has certain limitations: First, given that *tuina* therapy relies on the proficient mastery of techniques and acupoints by the practitioner, it is difficult to implement a blinded design. As a form of physical contact between the practitioner and the patient, *tuina* therapy, whether or not it targets specific acupoints, inevitably stimulates the skin, muscles, and peripheral nerves. Therefore, it is also challenging to blind the patients. Consequently, a sham *tuina* group was not included. However, relatively standardized operational protocols and procedures have been established, and all participating practitioners must strictly adhere to them in an effort to minimize such differences. Nevertheless, completely eliminating such differences is challenging. If subsequent analyses reveal that these differences significantly impact the results, they will be considered incorporating them into our analytical models to ensure the accuracy and reliability of our findings. Second, due to financial and human resource constraints, this study does not conduct a multicenter trial involving the entire country. Future work will aim to expand the scope of the study.

### Conclusions

This study will investigate the efficacy and safety of *tuina* therapy in the prevention and treatment of myopia in adolescents, providing evidence for clinical decision-making and supporting the inheritance and development of *tuina* therapy. It is noteworthy that previous studies have not investigated the intervention effects of *tuina* therapy on myopia from the perspective of TCM holistic philosophy. This study will be the first to explore the effects of *tuina* therapy on myopia in adolescents from the perspective of TCM holistic philosophy. This study could support *tuina* therapy as an effective method for managing myopia in adolescents, offering potential benefits to patients and their caregivers.
